### Risks of the Study

There are no major known risks to the study. Minor risks, such as black stains on the carious tooth surface or temporary stains on the skin, will occur. Temporary stains on the skin disappear within 48 hours without treatment.

### Withdrawal Criteria

During semiannual applications, clinical examination for caries will be done. If any pulpal involvement or abscess is noticed, appropriate treatment will be provided by the principal investigator. The children will be given the right to refuse or withdraw at any point in time.

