All tooth surfaces, including the buccal, lingual, mesial, distal, and occlusal surfaces for posterior teeth, are evaluated for caries. Miller’s criterion is used to assess whether active caries are present; Miller’s criterion suggests that a carious lesion is termed active if a blunt University of North Carolina–15 probe can easily enter it; a carious lesion is defined as halted when the dentine cannot be penetrated.

The size of the lesion is categorized as small or large at the tooth-surface level (less than one-third of the buccal, lingual, or occlusal surface, or less than half of the mesial or distal surface).

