### Outcome Measure

The primary outcome measure is caries arrest at the twelfth month of application of SDF. The secondary outcome measure is the caries increment (ie, CAST index).

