### Sample Size Estimation

Based on the previous studies, the anticipated proportion of sound occlusal surfaces at baseline that develop into cavitated dentin lesions at the 30-month follow-up is approximately 25% [3].

Sample size calculation was performed with G* Power 3 (Heinrich-Heine-Universität Düsseldorf). Based on a 5% level of significance, power of 80%, effect size of 0.63, and 3 groups, the required sample size is 120, including 40 in each group. Considering a drop-out rate of 20%, the final sample size is 150, as shown by the following equation: final sample size = ND = N / (1 – d), where *N* is the sample size before drop-out, *d* is the expected drop-out rate, and *ND* is the sample size considering drop-out. Thus, ND = 120 / (1 – 0.2) = 120 / 0.8 = 150, and the total sample required for intervention is 150 (50 in each group). The allocation ratio is 1:1:1. The participants are allocated to the 3 groups equally.

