### Statistical Analysis

Data analysis will be done using SPSS (version 23.0; IBM Corp). Continuous variables will be presented as the mean (SD). Categorical variables will be presented as frequencies and percentages. To confirm normality, the Shapiro-Wilk and Kolmogorov-Smirnov tests will be used. A one-way analysis of variance (ANOVA) statistical test will be used to compare the means of continuous outcome variables if the data follow a normal distribution. Nonparametric tests (ie, the Kruskal-Wallis statistical test) will be used in the data analysis in cases when there is skewed distribution of data. Post hoc tests will be performed with an ANOVA or the Kruskal-Wallis test.

Binary logistic regression will be performed. The dependent variable will be whether the lesion is arrested or not at the 12-month examination, and the independent variables will include the children’s oral hygiene habits (eg, tooth brushing), fluoride agent use (eg, fluoride toothpaste), dietary habits (eg, bottle feeding), and source of drinking water.

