### Ethical Considerations

Ethical approval has been obtained from the Institutional Review Board (Ethics Committee II) of Yenepoya (Deemed to be University) for protocol version 3 (YEC2/175). Research aides will serve as contact people and be involved in all phases of the trial. Parents or legal caretakers of the children are given an information sheet outlining the purpose of the study, the specifics of the research, and the processes after the principals consent to participate in the study. Parents are informed of the side effects of the treatment, notably staining of the tooth. Their queries regarding the side effects are addressed. Before beginning this trial, informed consent is obtained. The participants, including the children and their guardians, are free to withdraw at any time during the study. They are also allowed to pursue additional dental care according to their own decisions and financial means.

Caries assessment is done with aseptic precautions and without any harm to the patient. The application of 12% SDF, 30% SDF, or 38% SDF is also done with aseptic precautions and without any harm to the patient. If any complications take place, the child is treated free of charge by the principal investigator.

The study data will be deidentified for privacy and confidentiality protection. No compensation will be offered to the study participants.

The drugs were sponsored by Biodinamica. This drug company has no role in the research.

The Drug Controller General of India does not normally restrict the use of topically applied drugs. Currently, there are also no official guidelines announced for SDF use by dental professional associations or research bodies [10].

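### Lesions that reach the pulp or abscess and are treated before month 12 have no stated status in the arrest outcome, so they may be lost from the analysis or scored as halted

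*Protocol article*

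**What the plan says.** All references are to the protocol article.

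- **Withdrawal Criteria** begins "During semiannual applications, clinical examination for caries will be done" and continues "If any pulpal involvement or abscess is noticed, appropriate treatment will be provided by the principal investigator". Pulpal involvement and abscess are the only clinical events named there. The one explicit statement about leaving the trial is voluntary: "The children will be given the right to refuse or withdraw at any point in time".
- **Outcome Measure**: "The primary outcome measure is caries arrest at the twelfth month of application of SDF".
- **Baseline and Follow-up Oral Examinations** defines arrest by probing alone: "a carious lesion is defined as halted when the dentine cannot be penetrated". The same section gives CAST codes for restoration (2), pulpal involvement (6), abscess (7) and extraction for caries (8), but does not link them to arrest. Under Outcome Measure, CAST belongs to the secondary outcome.
- **Statistical Analysis**, on the logistic regression: "The dependent variable will be whether the lesion is arrested or not at the 12-month examination".
- **Ethical Considerations**, on families: "They are also allowed to pursue additional dental care according to their own decisions and financial means".
- **Sample Size Estimation**: "Considering a drop-out rate of 20%, the final sample size is 150".

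**The concern.** Participant Selection excludes pulpal exposure, swelling and fistula at baseline. Pulpal involvement or abscess of a study lesion is therefore progression after enrolment, the clearest way for arrest to fail. The protocol puts this event under a withdrawal heading and sends it to treatment, while the outcome rule needs an exposed lesion to probe at month 12. An extracted tooth cannot be probed. A restored or pulp-treated tooth has no exposed lesion, and read literally could pass as halted.

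Outside dental care, which the protocol permits, leads to the same gap. A logistic regression omits records with no outcome, so failures could leave the denominator alongside ordinary drop-outs. The 20% drop-out allowance protects the number analysed, not against loss caused by the outcome.

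At stake is the comparison between concentrations. The Introduction expects the lower concentrations to be comparable with 38%, and the Discussion expects 38% to be superior. A distortion in either direction would bear on one of these.

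**Working it through.** **The plan's own figure.** 120 / (1 − 0.2) = 150, as stated. This calculation concerns numbers only. The document gives no expected arrest rate and no rate of pulpal failure, so the rates below are assumptions.

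**When the event can occur.** Under Application of SDF, applications are at baseline and 6 months, with examinations at 6 and 12 months. Pulpal involvement is excluded at baseline, so the failures at issue are those found at about month 6, plus any treated outside the trial before month 12. A failure first seen at the month-12 examination is itself the outcome observation.

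**Formulas.** Let p be the true proportion arrested, and f the proportion of all lesions in the arm that reach the pulp or abscess and are treated before month 12. The f lesions are part of the 1 − p not arrested.

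- Counted as not arrested: p
- Dropped: p / (1 − f), with odds p / (1 − p − f)
- Scored as halted: p + f

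**Results for assumed true arrest of 50% (lower concentration) v 65% (higher).** The true odds ratio is (65/35) / (50/50) = 1.86.

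| Failures f, lower v higher | Arrest seen if dropped | Difference | Odds ratio if dropped | Difference if scored halted |
|---|---|---|---|---|
| none lost | 50.0% v 65.0% | 15.0 points | 1.86 | 15.0 points |
| 15% v 5% | 50/85 = 58.8% v 65/95 = 68.4% | 9.6 points | (65/30)/(50/35) = 1.52 | 70 − 65 = 5 points |
| 10% v 5% | 50/90 = 55.6% v 65/95 = 68.4% | 12.9 points | (65/30)/(50/40) = 1.73 | 70 − 60 = 10 points |
| 10% v 10% | 50/90 = 55.6% v 65/90 = 72.2% | 16.7 points | (65/25)/(50/40) = 2.08 | 75 − 60 = 15 points |

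**What sets the direction.** The inflation in an arm is p × f / (1 − f), so it depends on the arrest rate as well as the failure rate. On the odds-ratio scale, what matters is the share of non-arrested lesions removed. In the second row these shares are 15/50 = 30% v 5/35 = 14%, and the odds ratio falls. In the last row they are 10/50 = 20% v 10/35 = 29%, and it rises. If the same share s is removed in both arms, each arm's odds become p / ((1 − p)(1 − s)). The factor 1 − s cancels, and the odds ratio stays at 1.86.

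**No true difference.** With 60% arrest in both arms and 30% v 10% of non-arrested lesions removed, the rates seen are 60/(60 + 28) = 68.2% v 60/(60 + 36) = 62.5%. The lower concentration then looks better by 5.7 points, with an odds ratio of 28/36 = 0.78.

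These figures treat removal as lesion by lesion. If a whole child left the trial, that child's other lesions would go too, and the effect could differ.

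**The case against.** The strongest reply is that the text states treatment, not exclusion. A reader might infer from the heading that these children leave the trial and have no 12-month status. The sentence does not say so, and the only stated withdrawal is voluntary. This stands: loss from the analysis is a possibility the wording leaves open, not a rule it sets.

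Second, the data to classify these lesions are collected. CAST codes 2, 6, 7 and 8 exist, Adverse Effects provides oral examinations at 6 and 12 months with changes recorded, and a lesion that reached the pulp reads naturally as not arrested. This makes the repair easy, but the codes are not linked to the arrest outcome, and the probing definition gives no answer for a treated tooth.

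Third, handling of treatment before the endpoint and of missing data is commonly left to an analysis plan or full protocol, neither of which is shown. The absence of an imputation method would be no finding. The point here concerns what the article does fix: a failure of its primary outcome placed under withdrawal, and an outcome definition that cannot classify the tooth afterwards.

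Fourth, a reader might infer that the logistic model is where the concentrations are compared, or that losing failures always shrinks the difference. Neither is supported. Treatment group is not named among that model's independent variables, so the point concerns the 12-month arrest analysis in general. The last row of the table shows the difference widening.

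Finally, small lesions are enrolled and the window is mainly the first six months, so 15% failure may be high. The document gives no rate by which to judge this.

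**Conclusion.** The point holds as a defect in the outcome rule that should be fixed. The withdrawal section, the probing definition and the 12-month outcome do not together say what becomes of a lesion that fails and is treated before month 12. If such lesions are dropped or scored as halted, arrest is overstated in every arm where they occur, and the comparison between concentrations may be biased.

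Under assumed arrest of 50% v 65%, dropping failures changes the true 15.0-point difference to between 9.6 and 16.7 points in the cases examined. Scoring them as halted gives 5 to 15 points. The odds ratio changes only if the share of non-arrested lesions removed differs between arms. All these rates are assumptions. The documents do not support saying that these children are excluded, that bias is certain, or that it runs in one direction.

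**What to change.** Leave clinical care as it is and add an endpoint rule:

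- Children with these events stay in follow-up and are analysed in their randomised arm.
- Any baseline lesion that develops pulpal involvement or abscess (CAST 6 or 7), or is extracted or restored for caries before month 12 (CAST 8 or 2), counts as not arrested in the 12-month arrest analysis.
- The rule uses the 6-month record as well as the 12-month one, because a tooth coded 6 or 7 at month 6 may carry another code once treated.
- Only shed teeth and children lost to follow-up are treated as missing.

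Reconcile the Withdrawal Criteria heading with this rule, so that a clinical failure does not read as a reason to leave the trial.

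The cost is small: the examinations and codes are already planned, and reported arrest rates will be slightly lower. CAST 2 does not say why a tooth was restored, so the case report form should record the reason, and a restoration for a reason other than caries needs its own stated handling.

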### Maximum Dose and Safety Margin

The margin of safety for dosing is of paramount concern. The typical lethal dose, 50% (LD 50), for oral administration is 520 mg/kg. One drop (25 µL) contains 9.5 mg SDF and is sufficient to treat 5 teeth. The dose will be 0.95 mg/kg, and assuming that the smallest children with caries weigh between 10 kg and 15 kg, the relative safety margin for administering a whole drop to a child weighing 10 kg is therefore 380 mg/kg LD 50 / 0.95 mg/kg dosage, for a 400-fold safety margin. The actual dose will probably be much lower. One drop (25 µL) per 10 kg per treatment session is the suggested upper limit. The largest applied dose for 3 teeth is 2.37 mg, allowing for more than 400 applications [11].

### Adverse Effects

Information on adverse effects of SDF treatment—including tooth or gum pain, gum swelling, gum bleaching (ie, becoming whiter), and systemic toxicity (nausea, vomiting, and generalized discomfort)—is collected through a parental questionnaire within a week of SDF or placebo application at baseline and at 6- and 12-month follow-ups. If there is an acute systemic illness associated with SDF treatment, the parents are asked to immediately contact the principal investigator by telephone. Oral examinations will also be performed at baseline and at 6- and 12-month follow-ups. An examiner will evaluate the hard and soft tissues to establish changes and visible alterations during the clinical examination. All changes will be recorded on a case report form.

## Results

The research was funded in September 2020, and data collection started in September 2022. As of February 2023, 150 participants were enrolled in the study. The project is still underway and is expected to be completed in December 2023. The findings of this study will be beneficial for future studies and the management of early childhood caries.

The information obtained from the study will be submitted to the institution and to the concerned authorities. The details of the study will be published in journals and presented at conferences.

## Discussion

### Principal Aims

The purpose of this single-center, randomized, active-controlled, 3-arm pragmatic trial is to evaluate and compare the efficacy of 12%, 30%, and 38% SDF in preventing early childhood caries in children aged 24 to 72 months. We are using 38% SDF, which is thought of as the standard of care for preventing ECC, in a positive control group to determine if 30% and 12% SDF are superior.

Our hypothesis is that 38% SDF will have a superior effect compared to 30% and 12% SDF in stopping ECC, because it has a fluoride concentration that is much higher (44,800 ppm) than 30% (35,400 ppm) or 12% (14,100 ppm) SDF. The standard of care will be altered if the results are as expected. Because every child who enrolls in the study should have the right to obtain an efficient preventative strategy, there is no negative control group.

In this study, we evaluate the ability of 12%, 30%, and 38% SDF to arrest ECC. The use of SDF solutions in a clinical setting has been deemed safe, and the application process is noninvasive. Despite the fact that the participants in this study are recruited at a young age, few ethical questions have been raised.

In order to examine the efficiency of 12% and 38% SDF in halting dentin caries in the primary teeth of preschool children, Fung et al [8] undertook a randomized clinical experiment. Other recent research indicates that 38% SDF is more effective than 12% SDF. In a clinical trial, Vollú et al [12] compared the effectiveness of 30% SDF and atraumatic restorative treatment in halting dentine caries in the primary molars of preschoolers. Recent research revealed that 30% SDF could stop caries lesions with effects comparable to those of atraumatic restorative treatment.

The findings of this trial, performed in young children who are in good health, may not be generalizable to other populations of children, such as those who require special medical attention or are older, which is a limitation of this study. It will be necessary to perform additional research on the preventive impact of SDF in individuals with special health care requirements. The generalizability of the study will also be limited by the fact that clinical trials in different countries use different parameters for caries assessment.

The study outcomes will be widely disseminated, which should encourage the adoption of SDF in other nations and lessen the global burden of ECC. SDF may even become a crucial component of comprehensive and successful preventative programs to achieve the UN sustainable development goals.

### Conclusions

The findings of this study will be beneficial for future studies on the management and prevention of ECC. If SDF is found to be effective in a school or community setting for caries prevention, it will be a significant milestone for preventive dentistry.

## Appendix

Multimedia Appendix 1 Informed consent form given to parents.

## Abbreviations

ANOVA: analysis of variance
CARE: Consensus-Based Clinical Case Reporting Guideline
CAST: Caries Assessment Spectrum and Treatment
ECC: early childhood caries
SDF: silver diamine fluoride
WHO: World Health Organization
